#### Aim 3: Associations of Physical Function, PA, Personal and Environmental Factors, and QoL, and Moderation by Race and Ethnicity

To examine the associations among physical function, PA, personal and environmental factors, and QoL, multiple linear regression analyses will be performed with QoL as the dependent variable. The primary independent variables will include PROMIS-PF and habitual PA (steps per day), with additional personal and environmental factors entered as indicated by the conceptual model. Covariates such as sex and autism severity will be included as appropriate. We hypothesize that better physical function and greater PA will be associated with better QoL. To evaluate moderation by race and ethnicity, interaction terms between race/ethnicity and physical function, as well as between race/ethnicity and PA, will be entered into the regression models. Continuous predictors will be centered prior to the creation of interaction terms to improve interpretability and reduce multicollinearity. When significant interactions are identified, simple slopes or stratified analyses will be used to further characterize the nature of the moderation effect. Model results will be reported using unstandardized and standardized regression coefficients, 95% CIs, *P* values, and model fit statistics (eg, adjusted *R*^2^). The same a priori power analysis described above applies to aim 3; although this pilot study may be underpowered to detect small effects, it is expected to provide preliminary effect size estimates to guide future research [63].

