### Statistical Data Analysis Plan

All analyses will be conducted using 2-sided tests with a significance level of α=.05. Descriptive statistics will summarize participant characteristics and study variables. Continuous variables will be summarized using means and standard deviations or medians and interquartile ranges, as appropriate, and categorical variables using frequencies and percentages. Prior to inferential analyses, assumptions of normality, linearity, homoscedasticity, and absence of multicollinearity will be evaluated. If the assumptions for parametric analyses are not met, appropriate nonparametric or robust analytic methods will be applied.

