An a priori power analysis was conducted using G*Power (version 3.1.9.7; Heinrich Heine University Düsseldorf) [63]. Assuming a 2-tailed α=.05 and power=0.80, a total sample size of N=155 provides adequate power to detect small-to-moderate correlations (r ≥ 0.25-0.30), consistent with expected construct validity effect sizes. PROMIS-PF scores are expected to demonstrate moderate positive correlations with habitual PA and performance-based functional measures and moderate-to-strong positive correlations with other self-reported function scales. Negative correlations are anticipated with fall risk indicators and comorbidity burden. In addition to the power-based justification, precision was considered. At N=155, correlation estimates are expected to have reasonably narrow 95% CIs, supporting adequate precision in estimating associations [64].

The sample size for reliability analyses was informed by Borg et al [59]. Assuming 2 repeated measurements per rater, a subsample of n=25 is expected to provide sufficient precision to estimate ICC values ≥0.75, consistent with recommendations for reliability studies.

The full sample (N=155) will be used for primary construct validity analyses, while the nested subset (n=25) will support exploratory performance-based validity analyses and reliability estimation.

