### Strengths and Limitations

This protocol has several strengths. First, it integrates patient-reported, behavioral, and remotely observed indicators of physical function into a single telehealth-based study design. Second, it evaluates both construct validity and rating reliability, thereby strengthening the measurement framework for remote assessments in adults with ASD. Third, the protocol explicitly incorporates racial and ethnic disparities in physical function, PA, and QoL, which may inform future equity-focused research and intervention.

Several limitations should also be acknowledged. As a pilot study, the project may be underpowered to detect small effects, particularly in subgroup and moderation analyses. In addition, the sample includes independently living adults with relatively high cognitive abilities, which may limit generalizability to individuals with greater support needs. A further limitation is the overrepresentation of females in the SPARK registry relative to historical ASD diagnosis ratios, although more recent literature suggests that previous estimates of the male-to-female ratio may partly reflect underdiagnosis or delayed diagnosis in females [71-73]. Future studies should prioritize broader representation across sex, racial and ethnic background, cognitive profiles, and levels of required support. Finally, remote performance-based assessments may be influenced by the home environment, camera positioning, technology access, and participant familiarity with telehealth procedures. Accordingly, the primary contribution of this study is expected to be methodological and hypothesis-generating rather than definitive.

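### The N=155 correlation power analysis is said to apply to Aim 3, but it does not cover the race/ethnicity interaction tests, which are underpowered for moderate as well as small slope differences

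*Protocol article*

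**What the plan says.** The article contains one power calculation, under Aim 1. It sets the terms as "Assuming a 2-tailed α=.05 and power=0.80" and concludes that "a total sample size of N=155 provides adequate power to detect small-to-moderate correlations (r ≥ 0.25-0.30), consistent with expected construct validity effect sizes". The Statistical Data Analysis Plan fixes the same level for every test: "All analyses will be conducted using 2-sided tests with a significance level of α=.05".

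The Aim 3 section plans a multiple linear regression of quality of life (QoL) on PROMIS-PF and steps per day. It adds interactions of race/ethnicity with physical function and with physical activity. On power it says "The same a priori power analysis described above applies to aim 3", and the sentence continues "although this pilot study may be underpowered to detect small effects, it is expected to provide preliminary effect size estimates to guide future research". On follow-up it says "When significant interactions are identified, simple slopes or stratified analyses will be used to further characterize the nature of the moderation effect". Separately, the section commits to reporting coefficients with 95% CIs and P values, without conditions.

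Strengths and Limitations concedes that the project "may be underpowered to detect small effects, particularly in subgroup and moderation analyses", and describes the expected contribution as hypothesis-generating.

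No interaction effect size, group split or interaction power is given anywhere in the article.

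**The concern.** A correlation in the whole sample and a difference between two group slopes are different quantities with different standard errors. The first uses all 155 participants. The second compares two within-group slopes, and its variance is dominated by the smaller group. A calculation for the first says nothing about the second.

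Whether the relationships vary by race and ethnicity is part of one of the three primary aims listed under Objectives. A reader who accepts that the Aim 1 calculation carries over, with a reservation about small effects only, will suppose that moderate moderation would probably be found. If that is untrue, a non-significant interaction carries much less information than the article implies. The group-specific follow-up would then be seen mainly in the cases where the estimated difference happened to be large.

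**Working it through.** **Step 1. The plan's own figure.** Inputs: two-sided α=.05, power 0.80, N=155, r=0.25 and 0.30 (Aim 1). With Fisher's z, N = ((1.960 + 0.842)/atanh(r))² + 3.

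- r=0.25: N = 124; power at N=155 is 88%.
- r=0.30: N = 85; power at N=155 is 97%.

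The Aim 1 statement is true as worded. The question is only whether it transfers.

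**Step 2. Inputs for the interaction.** From the Recruitment part of the Results: 34 non-Hispanic White, 79 Black/African American and 40 Hispanic participants, so 34 against 79 + 40 = 119. The two-group contrast is the one the article gives for Aim 2; using it for Aim 3 is an assumption. The article gives no slopes, residual variance or predictor correlation, so these are also assumed and varied: standardized variables with equal SDs in the groups, residual variance s² from 0.60 to 0.91, and correlation ρ between PROMIS-PF and steps from 0 to 0.4.

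**Step 3. Power for a slope difference, 34 vs 119.** SE = s·√(1/(n₁−1) + 1/(n₂−1))/√(1−ρ²), with power from the noncentral t on n₁+n₂−9 degrees of freedom. Here √(1/33 + 1/118) = 0.197.

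- Most favourable case (s²=0.60, ρ=0): SE = 0.775 × 0.197 = 0.153.
- Least favourable case (s²=0.91, ρ=0.4): SE = 0.954 × 0.197/0.917 = 0.205.

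| Standardized slope difference | Power |
|---|---|
| 0.2 | 16-26% |
| 0.3 | 31-50% |
| 0.4 | 49-74% |
| 0.5 | 68-90% |

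The difference needed for 80% power runs from 0.43 to 0.58 across these cases, or roughly 0.45-0.6.

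**Step 4. Cross-check with two correlations.** Fisher's z: SE = √(1/31 + 1/116) = 0.202. For 0.5 vs 0.3, atanh(0.5) − atanh(0.3) = 0.549 − 0.310 = 0.240, and 0.240/0.202 = 1.19, giving 22% power. In the same way, 0.5 vs 0.2 gives 40%, 0.5 vs 0.1 gives 60% and 0.5 vs 0 gives 78%.

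**Step 5. Is it only the enrolled split?** The planned quotas were 50 Black and 50 Hispanic participants, which leaves at most 155 − 100 = 55 others. At 55 vs 100, SE = √(1/52 + 1/97) = 0.172, and the same four contrasts give 29%, 52%, 74% and 89%. Power for moderate differences was already low at the most balanced two-group split that the quotas allow.

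**Step 6. Other model forms.** Simulating the Aim 3 regression with both interactions, sex and autism severity (2,500 runs per scenario, activity slope assumed to be 0.2) gave 17-22%, 31-39%, 49-57% and 68% for slopes of 0.5 vs 0.3, 0.2, 0.1 and 0. A three-group omnibus test (34/79/40) did worse: 24-36% for differences of 0.3.

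**The case against.** The strongest defence is that the article already warns the reader. Aim 3 carries a pilot caveat, Strengths and Limitations names moderation specifically, and the work is called hypothesis-generating. This stands as far as it goes, but both caveats speak of small effects only, and differences of 0.3-0.4 fall short too.

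Second, the 34 vs 119 split was an outcome of recruitment and not a planning figure. That is fair, but Step 5 shows the shortfall at a planned-type split as well.

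Third, the Aim 3 numbers rest on inputs the article does not give. That is also fair, and is why only ranges are offered.

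Three stronger readings are tempting, and the article does not support them:

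- A reader might infer that even large moderation would be missed. Differences of 0.4-0.5 have about 49-90% power in the two-group model, so that goes too far.
- A reader might infer that group results are withheld unless significant. The unconditional promise of coefficients with 95% CIs covers the interaction term and the reference-group slope, and the other group's slope is their sum. Only the simple-slope or stratified follow-up depends on significance. What is lacking is chiefly a CI for the non-reference slope.
- A reader might infer that a null interaction will be reported as showing no moderation. Nothing in the article says so; it is a risk that the power sentence invites.

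**Conclusion.** The point holds as a matter of scope; there is no arithmetic error. The Aim 1 calculation is correct for simple correlations and serves as a rough guide for the Aim 3 main effects. It does not apply to the interactions. A difference of 0.3 between group slopes has about 31-50% power, against 97% for a whole-sample correlation of 0.30.

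The caveats should therefore extend to moderate moderation. The figures depend on two-group coding, standardized variables with equal spread, and the assumed residual variance and predictor correlation. Three-group coding would lower them, and a more balanced split would raise them.

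**What to change.** Keep the pilot caveat and the statement about preliminary effect sizes; both sit in the same sentence as the power claim, so that sentence should be amended and not deleted. Suggested substance:

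- The N=155 calculation covers simple correlations and is a rough guide for the Aim 3 main effects only.
- With 34 non-Hispanic White and 119 Black or Hispanic participants, the interaction tests reach 80% power only for standardized slope differences of about 0.45-0.6, with the assumptions listed alongside.
- Moderation analyses are exploratory, and a non-significant interaction will not be interpreted as equal slopes.
- Group-specific slopes with 95% CIs will be reported whatever the interaction P value, next to the interaction coefficient and CI already planned.

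Widen the matching caveat in Strengths and Limitations from small to small and moderate effects for moderation.

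The cost is a few sentences and one table of slopes. No new data are needed, and analysis is not projected to finish until July 2026.

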#### Missing Data

The extent and pattern of missing data will be examined before analysis, including missingness arising from incomplete wearable monitoring, partial remote assessment completion, technical disruptions during telehealth sessions, and unavailable registry-derived variables. If missing data are minimal, complete-case analyses will be used. If missing data are more substantial and judged to be consistent with a missing-at-random mechanism, multiple imputation may be considered as a sensitivity analysis for key multivariable models. Measure-specific completion rules (eg, Fitbit wear-time thresholds) will be applied before analytic inclusion. Any deviations from the primary analytic plan will be documented and justified.

## Results

### Overview

Funding for this study was active from August 2024 through May 2025. Participant recruitment was conducted from December 2024 to March 2025, and final data collection was completed in May 2025. As of May 2025, 155 participants had been recruited into the study. Figure 3 summarizes participant recruitment and enrollment. Data analysis is projected to be completed by July 2026, and the primary study results are anticipated to be submitted for publication in August 2026.

**Figure 3 figure3:**
[figure not shown]
Flow diagram of participant recruitment, eligibility, screening, and enrollment. ASD: autism spectrum disorder; PA: physical activity; QoL: quality of life; SPARK: Simons Powering Autism Research and Knowledge; SRS: Social Responsiveness Scale.

### Recruitment

Of 544 adults with ASD contacted through the SPARK Registry, 229 responded to invitation emails, and 227 expressed interest in participating (see Figure 3). Following the eligibility screening, 15 individuals were excluded, resulting in 212 eligible participants. Of these, 203 were invited to participate, and 155 ultimately provided electronic informed consent and were enrolled in the study. Among enrolled participants, 101 (65.2%) identified as female, 53 (34.2%) identified as male, and 1 (0.6%) selected rather not to say.

The sample was racially and ethnically diverse: 79 (51.0%) participants identified as Black/African American, 40 (25.8%) as Hispanic, 34 (21.9%) as non-Hispanic White, 1 (0.6%) as Asian, and 1 (0.6%) did not report race/ethnicity. Table 2 presents the participant demographic characteristics.

**Table 2 table2:** Sex and race/ethnicity of enrolled participants (N=155).

Sex	Non-Hispanic White, n (%)	Black/African American, n (%)	Hispanic, n (%)	Asian, n (%)	Did not report, n (%)	Total, n (%)
Male	9 (17.0)	19 (35.8)	25 (47.2)	0 (0.0)	0 (0.0)	53 (34.2)
Female	25 (24.8)	60 (59.4)	14 (13.9)	1 (1.0)	1 (1.0)	101 (65.2)
Rather not to say	0 (0.0)	0 (0.0)	1 (100.0)	0 (0.0)	0 (0.0)	1 (0.6)
Total^a^	34 (21.9)	79 (51.0)	40 (25.8)	1 (0.6)	1 (0.6)	155 (100.0)

^a^Values in the total row and column are presented as n (% of the total sample). Percentages may not sum to 100 because of rounding.

### Analysis Status

Data analysis is projected to be completed by July 2026. Submission of the primary results manuscript is anticipated in August 2026.

## Discussion

### Anticipated Principal Findings

This study is expected to generate preliminary evidence regarding the feasibility, validity, and equity relevance of remotely administered physical function and balance assessments in adults with ASD. If the planned hypotheses are supported, the study will demonstrate that patient-reported physical function is associated in the expected direction with related indicators of health and physical functioning, including PA, fall risk, lower-extremity functional outcomes, and comorbidity burden. The study is also expected to provide preliminary evidence regarding the reliability of rater scoring of recorded remote performance tasks and the feasibility of telehealth-delivered physical function assessments in adults with ASD.

### Comparison With Prior Work and Conceptual Rationale

This protocol represents, to our knowledge, the first attempt to systematically evaluate the reliability and validity of remote, performance-based physical function and balance assessments in adults with ASD. Prior work in other populations supports the relevance of combining patient-reported and performance-based measures. More recently, moderate-to-strong associations were demonstrated between PROMIS-PF and common performance-based measures such as the 5xSTS, Time Up and Go, and 10-Meter Walk Test in outpatient neurologic rehabilitation, highlighting the complementary value of these approaches [44]. However, that study was conducted using retrospective, in-clinic data and did not address feasibility, reliability, or validity in remote assessment contexts or in autistic populations [44]. By adapting standardized assessments for telehealth delivery, the present study addresses an important gap in rehabilitation research for neurodivergent populations and applies a prospective remote-assessment approach. Persistent motor impairments, including deficits in coordination, balance, and gait, remain underresearched in adults with ASD despite their relevance to fall risk, reduced PA, and diminished participation [65]. The protocol is grounded in the MHDD framework, which emphasizes the interaction among health conditions, functional status, activity, participation, and contextual factors in shaping QoL [25]. Within this framework, remote physical function assessment is positioned as a practical approach for identifying modifiable factors that may influence participation, PA, and health equity. Findings from this work are expected to help address the need for standardized, accessible, and psychometrically sound functional assessments that remain relevant across adulthood in ASD [66].

### Clinical and Research Implications

If the planned assessments are found to be feasible and psychometrically supported, this protocol has the potential to inform new models of physical therapy assessment for adults with ASD by enabling clinicians to administer standardized functional measures remotely. Such an approach may reduce barriers associated with transportation, sensory sensitivities, and anxiety, all of which can limit access to in-person services for adults with ASD [67,68]. These barriers may also contribute to reduced PA and increased fall risk. Telehealth-based assessment, combined with wearable activity monitoring, may therefore improve participation in both research and clinical care among individuals who might otherwise be underrepresented or unable to access physical therapy services. In addition, examining the relationship between remotely observed performance and patient-reported outcomes may strengthen clinical interpretation and support more individualized care planning.

### Advancing Health Equity

A central contribution of this protocol is its focus on health equity. Telehealth delivery aligns with broader efforts to reduce health care disparities among adults with ASD, particularly among racial and ethnic minority groups who often face additional structural barriers to care [69,70]. By evaluating the reliability and validity of remote physical function assessments, this study may help establish a foundation for more scalable and equitable rehabilitation strategies. Remote assessment may be especially beneficial for adults with ASD who experience anxiety, sensory overresponsiveness, or transportation barriers that make clinic-based participation difficult. Conducting assessments within the home environment may reduce these barriers by allowing participation in a setting that is familiar, controlled, and often more tolerable. If the proposed measures demonstrate acceptable performance, they may support more equitable access to observational physical assessments and provide clinicians with alternatives to relying exclusively on questionnaires. This work may also inform future intervention studies aimed at improving PA, physical functioning, and QoL in diverse adult ASD populations.

### Strengths and Limitations

This protocol has several strengths. First, it integrates patient-reported, behavioral, and remotely observed indicators of physical function into a single telehealth-based study design. Second, it evaluates both construct validity and rating reliability, thereby strengthening the measurement framework for remote assessments in adults with ASD. Third, the protocol explicitly incorporates racial and ethnic disparities in physical function, PA, and QoL, which may inform future equity-focused research and intervention.

Several limitations should also be acknowledged. As a pilot study, the project may be underpowered to detect small effects, particularly in subgroup and moderation analyses. In addition, the sample includes independently living adults with relatively high cognitive abilities, which may limit generalizability to individuals with greater support needs. A further limitation is the overrepresentation of females in the SPARK registry relative to historical ASD diagnosis ratios, although more recent literature suggests that previous estimates of the male-to-female ratio may partly reflect underdiagnosis or delayed diagnosis in females [71-73]. Future studies should prioritize broader representation across sex, racial and ethnic background, cognitive profiles, and levels of required support. Finally, remote performance-based assessments may be influenced by the home environment, camera positioning, technology access, and participant familiarity with telehealth procedures. Accordingly, the primary contribution of this study is expected to be methodological and hypothesis-generating rather than definitive.

### Future Directions

This protocol may provide a foundation for integrating telehealth into neurodiverse rehabilitation research and practices. If the planned psychometric and feasibility findings are supported, future studies should replicate these methods in larger and more heterogeneous cohorts, including a greater representation of males, individuals with varying cognitive abilities, and adults with greater support needs. Future studies should also examine the longitudinal relationships between anxiety, perceived fall risk, physical performance, and PA in adults with ASD. In addition, evaluating whether race and ethnicity moderate the relationships among physical function, PA, and QoL may yield important insights for developing more tailored and equity-oriented interventions in the future.

